#### Sample size calculation

The sample size calculation is performed with the program G*Power.^37,38^ It is
assumed that a reduction of 0.4 HbA1c % points (reduction from 8.0 to 7.6)
and an HbA1c standard deviation from 0.8 in the CG and 1.0 in the IG are
present. This assumption is based on the previous results of the analysis of
the AOK START (Systematic Trial with Analysis of Results in Telemedicine)
Project.^10,39^ This resulted in an effect size of 0.6625 and a
power of 0.95. With this assumption, a sample size of 77 participants in
each group (total of 154; dropout already included) will be necessary to
show a significant effect. A 20% drop-out rate is estimated based on the
experience of a previous study.^
34
^

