**Methods::**

The DAVOS study is a 6-month-period prospective, multicentric, randomized
controlled trial. In total, 154 diabetes patients (age ≥18; treated with
insulin) will be recruited and randomized into control group or intervention
group. Both groups will receive standard diabetes care. The intervention
group will additionally use a diabetes app. HbA1c value will be monitored on
three separate defined visits. Primary endpoint is the overall reduction of
HbA1c value. Secondary endpoints (eg, usability of the app) will be
determined through patient-reported outcome questionnaires.

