### Intervention

Both groups are offered standard diabetes therapy, as they should not experience
any deficiency in professional care. All participants are encouraged to measure
blood glucose (BG) ideally before meals, two hours after meals, and before going
to bed, but at least three times a day during the entire study. The customer
service for telephone support will be available at any time.

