### Statistical Analyses

An overview of statistical methods is given here, which can be adapted depending
on the data situation at the end of the study.

First of all, a summary of baseline data (eg, laboratory and anamnestic data) is
essential. Including the 95% confidence interval, categorical variables are
presented in absolute and relative frequencies and continuous variables are
described by the number of participants, mean, standard deviation, standard
error, median, minimum, and maximum.

Parametric and nonparametric tests will be used to compare quantitative variables
and frequency, and the chi-square test is applied on qualitative variables.
Furthermore the Kolmogorov-Smirnov test will be applied as a test of normal
distribution.

We expect the changes in HbA1c value in this study to follow a normal
distribution (based on previous other studies).^
34
^

Analysis of variance (ANOVA) is the main statistical method to analyze the effect
of the DHA on HbA1c as primary endpoint to show whether there is a significant
difference in primary outcomes between the two treatment groups.^
35
^ Data from both Visit 2 and Visit 3 will be compared with baseline data
from Visit 1. In addition, an ANOVA with repeated measures is performed, and
differences between participants as well as the number of visits and a possible
interaction between treatment and number of visits are represented by the linear
model.

Assuming a significance level of .05, ANOVA can be used to check whether the null
hypothesis can be rejected and which alternative hypotheses (Table 2) can be
accepted. Possible correlations are determined using the Pearson correlation
coefficient.

For multiple imputation of missing data, the jump-to-reference (J2R) method is
used, among others. To impute missing single HbA1c values, data from the
patient’s file of the treating HCP can be used as a substitute (as well as from
DHA of the IG). If no values are available here, the “Last mean carried forward”
method can be used.^
36
^

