## Discussion

The hypothesis to be investigated in this study is that the use of a DHA has a
greater impact on the treatment of diabetes and improving glycemic control than
standard therapy. For patients, this could mean a great relief in everyday life and
improved support in managing their disease.

It is theorized that the provided self-management support, increased motivation, and
structured monitoring will have a positive impact on HbA1c levels, frequency of
hypoglycemia and hyperglycemia, and mental health.

Through interoperable procedures, patients can be optimally supported during the
study. Including the HCP in the study is beneficial because patients get to know
about the intervention in their usual setting, that is, routine physician
consultation. This way, there is no additional burden of the study, which could skew
results, and in addition, HCPs also learn how to use the DHA system and integrate it
into their daily practice.^
5
^

With regard to the current study design, it should be noted that an unblinded RCT
design risks biasing the results by various factors. First, selection bias could
arise because recruitment is unblinded in physicians’ offices. Selection bias is
mitigated by randomization, but, for example, patients who are not very compliant
could already be rejected by the physician.^
40
^ To avoid this, HCPs and practice staff are briefed before recruitment and
will receive a checklist of inclusion criteria listed by importance.

As the CG is not allowed to use the DHA, these participants also denied its potential
benefits. This could lead to an ethical dilemma as a risk of unblinding.^41,42^ Recent
studies have uncovered the problem that complete blinding is not possible in studies
including a CG to test a digital application.^
43
^

To compensate for these disadvantages and to minimize the suspected bias, it is part
of the closure management to invite the CG to use the DHA after completion of the
study.

However, if there is an effect from the intervention on the behavior of the CG, this
would underestimate the effect of the DHA rather than overestimate a positive effect.^
44
^

The usefulness and perceived usability are particularly crucial for the acceptance of
the proposed digital application and to improve patient compliance.^
45
^ On this point, the difficulty of defining “digital literacy” (see inclusion
criteria of Table 1)
appears. Participants should have a basic knowledge of computers and smartphones,

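### The sample size does not say whether its 0.4-point HbA1c reduction is a difference between arms; even if it is, the stated inputs give about 68% power after dropout, not 95%

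*Protocol article*

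**What the plan says.** The Sample size calculation section bases the trial on an assumption taken from an earlier telemedicine project. It is "assumed that a reduction of 0.4 HbA1c % points (reduction from 8.0 to 7.6"), with "an HbA1c standard deviation from 0.8 in the CG and 1.0 in the IG". From this it reports "an effect size of 0.6625", a power of 0.95, and 77 patients per group (154 in total), with 20% dropout already included. It gives no HbA1c change for the control group and does not say to which arm or time point the values 8.0 and 7.6 belong.

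The Statistical Analyses section names ANOVA as the main method, to test for a "difference in primary outcomes between the two treatment groups". Table 2 states H1 as superiority over standard care, and its footnote sets the clinically meaningful difference at 0.3 HbA1c percentage points. The abstract uses the language of change over time: "Primary endpoint is the overall reduction of" HbA1c.

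**The concern.** A test between two arms is planned on the difference between them: the intervention change minus the control change, or equivalently under randomisation the difference in follow-up means. The sample size section gives a figure worded as a fall and leaves the control side blank. If the 0.4 is what one treated group achieved over time, it is not yet the quantity that the ANOVA tests.

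Some control improvement is plausible. Patients enter on an HbA1c between 7.5% and 11.0%, both arms attend trial visits on top of usual care, and all participants are encouraged to self-test "at least three times a day during the entire study". The Discussion accepts that control behaviour may change and that the effect would then be underestimated, but nothing of this reaches the sample size.

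The stated power of 0.95 is also the figure a reader will use to interpret a null result. If the real power is much lower, a non-significant outcome could be misread as evidence that the app does not work, in a trial meant to support its official listing in Germany.

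**Working it through.** **Inputs (protocol article)**
- Reduction 0.4; SD 0.8 (CG) and 1.0 (IG); effect size 0.6625; power 0.95; 77 per group; dropout 20%: Sample size calculation.
- Significance level .05, between-group ANOVA: Statistical Analyses. Sidedness is not stated. With two groups, ANOVA is equivalent to an unpaired t-test.

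**Step 1. Reproduce the stated sample size.** Two-sample t-test with the noncentral t distribution, equal allocation, d = 0.6625, power 0.95:
- Two-sided .05: 61 per group (power 0.952). 61 / (1 − 0.20) = 76.25, rounded up to 77. This matches the plan exactly.
- One-sided .05: 51 per group. 51 / 0.80 = 63.75, rounded up to 64. No match.

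So 77 per group is a two-sided calculation at d = 0.6625.

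**Step 2. Does 0.6625 follow from the stated inputs?**
- Pooled SD = √((0.8² + 1.0²) / 2) = √0.82 = 0.9055.
- d = 0.4 / 0.9055 = 0.4417. With either SD alone: 0.4 / 0.8 = 0.50, or 0.4 / 1.0 = 0.40.
- Working back: 0.6625 × 0.9055 = 0.60. The effect size entered corresponds to a between-arm difference of 0.60, which is 1.5 times the stated 0.4.
- For 0.4 to give 0.6625, the SD would have to be 0.4 / 0.6625 = 0.604, below both stated SDs.
- A paired (before-after) calculation does not explain it either. It would need a correlation of about 0.80, which is not stated, and would give 32 patients, not 61.

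**Step 3. Power at the differences the text can support.** Two-sided .05, SD 0.9055, noncentrality d√(n/2). Evaluable per arm: 77 × 0.80 = 61.6, taken as 61.

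| Between-arm difference | How it could arise | d | Power, 61 per arm | Power, 77 per arm |
|---|---|---|---|---|
| 0.60 | implied by d = 0.6625 | 0.66 | 95% | 98% |
| 0.40 | 0.4 is the arm difference, or 0.4 is an IG fall with no CG fall | 0.44 | 68% | 78% |
| 0.30 | IG fall 0.4, CG fall 0.1; also the H1 threshold | 0.33 | 44% | 53% |
| 0.20 | IG fall 0.4, CG fall 0.2 | 0.22 | 23% | 28% |

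Taking 62 evaluable instead of 61 changes these by less than one percentage point. A one-sided test at .05, which the plan's own number does not fit, would give 78% (61 per arm) and 86% (77 per arm) at 0.40, still below 95%.

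**Step 4. Separate the two causes.** The loss from 95% to 68% comes wholly from 0.4 not giving 0.6625, and needs no assumption about controls. Only the loss below 68% depends on a control fall, and the control falls of 0.1 and 0.2 are assumptions.

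**The case against.** The strongest defence is that the SDs are given by arm in the same sentence, so 8.0 and 7.6 may be the values expected in CG and IG. The 0.4 would then already be net of any control change. This reading is open. The source project that could settle it is not reproduced in the document. It removes the control-change problem but not the arithmetic: 0.4 as an arm difference still gives d = 0.44 and 68% power.

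Three stronger readings are tempting, and the documents do not support them.

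- **That 77 per group was computed from 0.4.** It was not. It reproduces only from d = 0.6625, a difference of 0.60 on the stated SDs.
- **That the plan assumes no change in controls.** Silence is not an assumption of zero. If IG falls by 0.4, a difference of 0.60 would even imply that controls rise by 0.2.
- **That the design will lower control HbA1c and so cut the effect.** No control-change figure is given. The Discussion's statement that "structured monitoring will have a positive impact on HbA1c levels" sits in an account of what the app is hoped to achieve, and does not show that diary testing by controls lowers HbA1c. Entry selection, self-testing and extra visits act on both arms, and shared influences cancel in a randomised comparison. They erode the planned effect only if the source project's 0.4 already contained them, which cannot be seen. Nor can regression to the mean be quantified, because the document gives no source-population mean, SD or visit-to-visit correlation.

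It is also fair to say that the Discussion discloses the direction of the risk from changed control behaviour. It does not disclose the size or carry it into the power.

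**Conclusion.** The point holds in this form. The planning effect is not defined as a contrast between arms, no control change is stated, and the stated inputs do not deliver the stated power. On the reading most favourable to the plan, power is about 68% with 61 evaluable per arm and 78% if all 77 are evaluable, against a stated 95%. If the 0.4 is a single-arm fall that already contains improvement controls would also show, power is lower: 44% at 0.3, the difference that H1 itself calls clinically meaningful, and 23% at 0.2, both with 61 per arm.

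The first result rests on the stated SDs applying to the analysed outcome, a two-sided .05 test and 20% dropout. The section does not say whether the SDs are of HbA1c values or of HbA1c change. A smaller SD of change would raise power, but none is given. The further losses rest on an assumed control fall and show a range, not an estimate.

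**What to change.** Rewrite the Sample size calculation paragraph as follows:

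1. Define the planning effect as the between-arm difference in mean HbA1c change from baseline to day 180, and say which arm and time point the values 8.0 and 7.6 refer to.
2. State the assumed control change. Take it from the source project if that project provides one; otherwise show 0, 0.1 and 0.2.
3. Recompute the effect size from that difference and the SDs, and say whether the SDs are of HbA1c values or of change. State that the test is two-sided, if that is intended.
4. Replace the single 0.95 with the power of 77 per group after 20% dropout at those differences. With the present SDs and an intervention fall of 0.4, this is 68%, 44% and 23% for control falls of 0, 0.1 and 0.2.

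The cost is one rewritten paragraph and a less favourable stated power. No extra patients are proposed, and the conduct of the trial does not change.

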## Methods

### Trial Design

A prospective, multicentric, randomized controlled trial (RCT) will be conducted
over a period of 6 months to investigate the effect of a DHA on HbA1c levels in
patients with type 1 and type 2 diabetes mellitus. To this end, we will compare
two groups of patients fulfilling the inclusion criteria (see Table 1): The control
group (CG) will only receive the standard diabetes care and the intervention
group (IG) will additionally use the DHA to monitor diabetes-relevant values
using various graphs and observe potential changes in these endpoints. Each
group will consist of at least 77 patients and will be supervised for a minimum
of 180 days. The schematic design of the DAVOS trial (E**V**aluation
**O**f the Impact of E**S**ysta on Hba1c in Patients with
Type 1 and Type 2 Diabetes mellitus in **DA**ily practice) is shown in
Figure 1.

**Table 1. table1-19322968221075333:** Inclusion and Exclusion Criteria in the DAVOS Trial.

*Inclusion criteria*
• Diabetes mellitus type 1 or 2 • ≥18 years old • Treated with insulin • HbA1c at baseline ≥7.5% and ≤11.0% • Not having used the investigated DHA in the past 12 months • Willing to use a smart glucometer and/or smart insulin pen • Internet access, smartphone/computer compatible with the DHA • Digital literacy to use a smartphone adequately
*Exclusion criteria*
• Using other apps linked to a BG meter or using an insulin pump or continuous glucose monitoring • Having used the investigated DHA in the past 12 months • <18 years old • Impairments (also mental impairments, eg, psychotic disorders) • Patients with home nursing (assisting BG testing) • Current participation in a weight loss program • Current participation in another study • Steroid therapy within the past three months (no exclusion criterion if used topically or inhaled less than five times a week) • Blood pressure ≥200 mm Hg at screening • BMI ≥40 kg/m² • Anemia (according to the WHO definition^ 15 ^) • GFR ≤40 mL/min • Current or planned pregnancy, breastfeeding women • Alcohol or drug abuse (within the past three months) • Employees of Emperra GmbH E-Health Technologies (or other institutions being involved in the trial)

Abbreviations: BG, blood glucose; BMI, body mass index; DHA, digital
health application; GFR, glomerular filtration rate; WHO, World
Health Organization.

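### The stated effect size of 0.6625 does not follow from a 0.4-point difference with SDs of 0.8 and 1.0; it corresponds to 0.6 points, and 77 per group is sized for that

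*Protocol article*

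**What the plan says.** All inputs and outputs of the calculation are in one paragraph of the protocol article, Sample size calculation.

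- Difference: "assumed that a reduction of 0.4 HbA1c % points (reduction from 8.0 to 7.6". The text does not say whether this is a fall within the intervention group or a difference between groups.
- Variability: "and an HbA1c standard deviation from 0.8 in the CG and 1.0 in the IG are". The text does not say whether these are SDs of HbA1c levels or of change in HbA1c.
- Effect size and power: "This resulted in an effect size of 0.6625 and a". The power given with it is 0.95.
- Sample size: 77 per group, described in these words: "each group (total of 154; dropout already included) will be necessary to".
- Dropout: "A 20% drop-out rate is estimated based on the". The source named for it is an earlier study.

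The Trial Design section repeats the number as a minimum: "group will consist of at least 77 patients and will be supervised for a minimum". The Statistical Analyses section gives the significance level without saying whether the test is one- or two-sided: "Assuming a significance level of .05, ANOVA can be used to check whether the null". It names ANOVA as the main method for the primary endpoint, which for two groups is the two-sample t test. Measures and Questionnaires defines the primary endpoint as change in HbA1c.

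**The concern.** The effect size is presented as the result of the difference and the SDs given just before it. Dividing 0.4 by any SD that those two values can supply does not come near 0.6625. So either the difference that drove the calculation is not the one printed, or the effect size is wrong for the one printed.

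This paragraph is the article's only justification for 154 patients, and the 95% power attached to the primary endpoint rests on it. A reader who takes 0.4 points as the planned between-group effect would believe that the trial misses such an effect one time in twenty. On the printed SDs the chance would be roughly one in three after the planned dropout. The reader also cannot tell whether the trial was planned for 0.4 or for 0.6 points, which matters when a non-significant result has to be interpreted.

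**Working it through.** **Inputs.** From Sample size calculation: difference 0.4; SDs 0.8 and 1.0; effect size 0.6625; power 0.95; 77 per group; dropout 20%. From Statistical Analyses: alpha .05 and a two-group ANOVA. Assumption: two-sided test, tested in step 2.

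**Step 1: effect size.** d = difference / sqrt((SD1² + SD2²)/2).

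- Pooled SD = sqrt((0.64 + 1.00)/2) = 0.9055.
- 0.4 / 0.9055 = 0.4417, not 0.6625.
- With a single SD: 0.4/0.8 = 0.50; 0.4/0.9 = 0.44; 0.4/1.0 = 0.40. None reaches 0.6625.
- Back-solving: 0.6625 × 0.9055 = 0.600, and 0.6/0.9055 = 0.6626, which agrees with the stated value to within one unit in the fourth decimal.

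**Step 2: does the stated sample size follow from 0.6625?** Two-sample t test (noncentral t), 95% power:

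- Two-sided .05: 60 per group gives 0.9494 and 61 gives 0.9525, so 61 are needed. 61/(1 − 0.20) = 76.25, rounded up to 77. This is the stated number.
- One-sided .05: 51 per group, and 51/0.8 = 63.75, rounded up to 64. This does not match.

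So 77 per group is reproduced exactly from d = 0.6625 with a two-sided test and 20% dropout. That is the basis for inferring that the test is two-sided.

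**Step 3: power at the printed 0.4 points**, taking it as the between-group difference and the SDs as those of the analysed outcome (d = 0.4417):

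| Evaluable per group | Two-sided power | One-sided power |
|---|---|---|
| 61 (after 20% dropout) | 0.677 | 0.783 |
| 77 (no loss) | 0.777 | 0.861 |

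All four values are below 0.95. For scale, 95% two-sided power at d = 0.4417 takes 135 evaluable per group, or 135/0.8 = 168.75, rounded up to 169.

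**Step 4: if the SDs are of levels and change scores are analysed.** The SD of change is SD × sqrt(2(1 − r)), where r is the correlation between baseline and follow-up (assumed, because the article gives none; equal SDs at the two visits are also assumed). For 0.4 points at 61 per group, two-sided:

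| r | SD of change | d | Power |
|---|---|---|---|
| 0.3 | 1.071 | 0.373 | about 53% |
| 0.5 | 0.906 | 0.442 | about 68% |
| 0.7 | 0.701 | 0.570 | about 88% |

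At r = 0.5 the factor sqrt(2(1 − r)) equals 1, so the 68% in step 3 is also the change-score result for that correlation.

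**The case against.** The strongest objection is that the contradiction does not show which figure is wrong. A reader might infer that the trial simply has 68% power and is underpowered. The documents do not support that. The words describing the reduction from 8.0 to 7.6 read most naturally as a fall within one group. If the intended contrast was 0.6 points, for example a 0.4-point fall with the intervention and a 0.2-point rise in the control group, then 154 patients do give 95% power, and the fault is an input left out of the text. That a difference of 0.6 was entered into the software is likewise an inference from back-solving, since the software input is not shown. This objection stands, and the point is limited accordingly.

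A second objection is that an analysis using baseline values could turn 0.4 points into d = 0.6625. It could, but only with a baseline correlation of about 0.745 under covariate adjustment, or about 0.778 for change scores. The article states no correlation, calls the SDs simply HbA1c SDs, and names ANOVA. An exact match with 0.6 divided by the pooled SD would then be a coincidence. The objection does not remove the contradiction, but it does show that power at 0.4 points depends on an unstated quantity.

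Third, counting only 61 per group assumes that dropouts contribute nothing, whereas Statistical Analyses plans substitution from patient files and multiple imputation. That is a fair reason to quote 68-78% rather than 68% alone. Even the upper figure, with every patient fully informative, is well short of 95%.

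**Conclusion.** The paragraph is internally inconsistent, and nothing elsewhere in the article repairs it. The printed difference and SDs give d = 0.44; the printed 0.6625 belongs to 0.6 points, and the sample size was derived from 0.6625. With the stated SDs, 77 per group is therefore sized for 0.6 points and not for 0.4.

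The consequence for power is conditional. It is about 68% (61 evaluable per group) to 78% (77 per group) if 0.4 points is the between-group difference, the SDs are those of the analysed outcome, and the test is two-sided. If change scores are analysed and the SDs are of levels, power at 61 per group could be lower or higher than 68%, depending on the correlation (about 53% to 88% for r from 0.3 to 0.7). It is 95% if 0.6 points was the intended between-group difference. What can be said without conditions is that the stated 0.4 points, SDs, effect size and 95% power cannot all stand together as written.

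**What to change.** Reconcile the difference, SDs, effect size, power and sample size in the Sample size calculation paragraph. Say whether the assumed difference is between groups, whether the SDs are of HbA1c levels or of change (with the assumed correlation if one is used), and that the test is two-sided if that is so. Then take one of two routes:

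- Keep 0.4 points as the between-group difference, correct the effect size to 0.44, and restate power as about 68% with 61 evaluable per group and 78% with 77. If the SDs turn out to be of levels and change is analysed, recompute these figures with the assumed correlation.
- State that 154 patients give 95% power only for a between-group difference of 0.6 points, and justify 0.6, including what is assumed for the control group.

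Which route is right depends on the source data for the assumption, which only the sponsor can check. The cost is rewriting one paragraph. No extra patients are needed; the only downside is a less favourable stated power or a larger stated detectable difference.

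### The stated 0.95 power keeps the full effect after 20% drop-out, but jump-to-reference, the one multiple-imputation method named, dilutes the effect by whatever share it imputes

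*Protocol article*

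**What the plan says.** All references are to the Protocol article.

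- **Sample size calculation, inputs.** The difference is given as "assumed that a reduction of 0.4 HbA1c % points (reduction from 8.0 to 7.6". The spread in each group follows: "and an HbA1c standard deviation from 0.8 in the CG and 1.0 in the IG are".
- **Sample size calculation, result.** The standardised effect comes first: "This resulted in an effect size of 0.6625 and a". Power and group size are stated next: "power of 0.95. With this assumption, a sample size of 77 participants in". A parenthesis then says that the number allows for drop-out: "each group (total of 154; dropout already included) will be necessary to".
- **Sample size calculation, drop-out.** The rate is "A 20% drop-out rate is estimated based on the", with an earlier study as its source.
- **Statistical Analyses, test.** The alpha and method are given in "Assuming a significance level of .05, ANOVA can be used to check whether the null". Sidedness is not stated.
- **Statistical Analyses, missing data.** The method is introduced by "For multiple imputation of missing data, the jump-to-reference (J2R) method is", in a sentence that goes on to present J2R as one approach of several. For single missing HbA1c values, the treating practice's file (or, in the intervention group, the app) may supply a substitute. Failing that, last mean carried forward may be used.

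The sample size section does not adjust the effect for patients imputed by J2R.

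**The concern.** The two sections treat the same patients differently. In the sample size, a drop-out is removed and the rest are compared at the full assumed effect. Under J2R, the drop-out stays in the analysis. A missing outcome in the intervention group is drawn from the control-group distribution, so that patient contributes no expected treatment difference.

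The power statement and the J2R analysis therefore refer to different expected contrasts. The trial is meant to support certification of the app, and Table 2 sets 0.3 HbA1c points as clinically meaningful. A reader who expects the full assumed effect could take a smaller J2R estimate as evidence against the app, when the plan's own drop-out assumption would predict it.

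**Working it through.** **1. Reproduce the plan's figure.** Inputs: d = 0.6625, power 0.95, alpha .05, drop-out 20%. For a two-sample t-test, two-sided:

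- 60 per group gives power 0.949; 61 per group gives 0.9525. So 61 are needed.
- 61 / (1 − 0.20) = 76.25, rounded up to 77. This matches.
- One-sided testing needs 51, and 51 / 0.8 = 63.75, rounded up to 64. This does not match.

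The stated 77 is therefore 61 evaluable patients per group at the full effect, inflated for loss.

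**2. Find the raw difference behind 0.6625.** Pooled SD = √((0.8² + 1.0²)/2) = √0.82 = 0.9055.

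- 0.6625 × 0.9055 = 0.60 points.
- The stated 0.4 points gives 0.4 / 0.9055 = 0.44, and power 0.68 with 61 per group.

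This is a separate inconsistency, so both differences are carried below.

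**3. Expected contrast under J2R.** With a share p of the intervention group imputed from the control distribution, the expected contrast is (1 − p) × δ. At p = 0.20:

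- 0.8 × 0.60 = 0.48 points
- 0.8 × 0.40 = 0.32 points

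**4. Power under J2R with Rubin's rules.** Simulation: 2,000 trials, 30 imputations, 77 per group, 20% missing at random in each group, SDs 0.8 and 1.0, one endpoint, no baseline covariate, two-sided .05.

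| True difference | Mean J2R estimate | J2R power | Power with 61 completers |
|---|---|---|---|
| 0.6 | 0.478 | 0.887 | 0.95 |
| 0.4 | 0.316 | 0.52 | 0.68 |

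With exactly 15 of 77 missing per group (19.5%), the J2R powers are 0.91 and 0.54.

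**5. Sensitivity to the variance method (0.6 points, 20% imputed).**

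- Imputed values counted as fully observed: effect 0.8 × 0.6625 = 0.53 with 77 per group gives power 0.905.
- Completer information only, 61 to 62 per group at 0.53: power about 0.83.
- Repeated-sampling variance: SE = 0.8 × √((1.0 + 0.64)/61.6) = 0.1305. Then 0.48 / 0.1305 = 3.68, and power is Φ(3.68 − 1.96) = 0.957. Estimate and SE shrink by the same factor, so the test is as strong as in completers.

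**6. Sensitivity to the share imputed (0.6 points).**

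- 15% imputed: power 0.89 to 0.93.
- 10% imputed: power about 0.955 (range 0.94 to 0.96).

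**The case against.** The strongest reply is that the protocol does not commit the primary analysis to J2R for the whole 20%.

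- **J2R is one method of several**, and the section opens by allowing methods to be adapted to the data. This stands. J2R is still the only multiple-imputation method named. Record substitution and last mean carried forward are described for single missing values, not clearly for patients who leave.
- **Drop-out is not the same as a missing HbA1c.** Patients remain under their own physician, whose files may fill the gap. This stands, and at 10% imputed the shortfall has gone.
- **The variance method is not given**, which is normal for a protocol. This stands too: the power loss depends on Rubin's variance, although the dilution of the estimate does not.
- **A repeated-measures analysis is also planned.** A patient lost after Visit 2 still contributes Visit 2 data, so an effect across visits would be diluted by less than 20%.
- **The 0.4 points come from an earlier project.** Whether that figure already includes people who stopped using the system cannot be seen here. If it does, a further factor of 0.8 would count the dilution twice.

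A reader might infer that the planned analysis will estimate 80% of the effect, or that J2R reduces the power from 0.95 to about 0.52. The documents support neither. The first needs every drop-out to be imputed by J2R. In the second, most of the fall (0.95 to 0.68) comes from the mismatch between 0.6625 and 0.44, and only the step from 0.68 to about 0.52 belongs to J2R.

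**Conclusion.** The point holds conditionally. The drop-out arithmetic is correct for a completers' comparison. What does not follow is that 0.95 is also the power of an analysis using the named imputation at the plan's own drop-out rate.

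At 20% imputed by J2R with Rubin's variance, the expected difference falls by a fifth. Power at the implied 0.6 points is then about 0.89, a loss of about 6 percentage points. The loss disappears if record substitution brings the imputed share to about 10%, or if a repeated-sampling variance is used. In both cases the estimate is still diluted in proportion to the share imputed.

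How close the diluted estimate comes to the 0.3-point threshold depends on which effect is meant: 0.32 if 0.4 points is intended, but 0.48, well clear of it, if 0.6 points is intended. The effect-size inconsistency is the larger problem and has to be settled first. Correcting it alone would still leave a power figure for a completers' comparison, not for J2R.

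The figures assume equal missing shares in both groups, a single endpoint and no baseline covariate.

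**What to change.** In the Sample size calculation section:

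1. Reconcile the effect size: 0.4 points with SDs 0.8 and 1.0 gives about 0.44, while 0.6625 corresponds to 0.6 points.
2. Restate the expected difference and power for the imputation-based analysis of all 77 per group. State the share assumed to be imputed by J2R after record substitution, and the variance method. At 20% imputed with Rubin's rules, the entries would be an expected 0.48 points with power about 0.89 if 0.6 points is intended, or an expected 0.32 points with power about 0.52 to 0.54 if 0.4 points is intended.
3. Replace the remark that drop-out is already covered with a statement that patients with missing values are retained and imputed from the reference-arm distribution. It should say distribution and not mean, because J2R draws values and does not insert a single figure.

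The cost is a change of wording and one rerun of the power calculation. The stated power is likely to be less favourable; whether it is acceptable is for the sponsor to decide.
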